## Abstract

**Background:**

Up to 70% of breast cancer patients report symptoms of insomnia during and after treatment. Despite the ubiquity of insomnia symptoms, they are under-screened, under-diagnosed and poorly managed in breast cancer patients. Sleep medications treat symptoms but are ineffective to cure insomnia. Other approaches such as cognitive behavioral therapy for insomnia, relaxation through yoga and mindfulness are often not available for patients and are complex to implement. An aerobic exercise program could be a promising treatment and a feasible option for insomnia management in breast cancer patients, but few studies have investigated the effects of such a program on insomnia.

**Methods:**

This multicenter, randomized clinical trial evaluate the effectiveness of a moderate to high intensity physical activity program (45 min, 3 times per week), lasting 12 weeks, in minimizing insomnia, sleep disturbances, anxiety/depression, fatigue, and pain, and in enhancing cardiorespiratory fitness. Patients with breast cancer be recruited from six hospitals in France and randomly allocated to either the “training” or the “control” group. Baseline assessments include questionnaires [Insomnia Severity Index (ISI), Pittsburgh Sleep Quality Index questionnaire (PSQI), Hospital Anxiety Depression Scale (HADS), Epworth Sleepiness Scale (ESS)], home polysomnography (PSG), and 7-day actigraphy coupled with completion of a sleep diary. Assessments are repeated at the end of training program and at six-month follow-up.

**Discussion:**

This clinical trial will provide additional evidence regarding the effectiveness of physical exercise in minimizing insomnia during and after chemotherapy. If shown to be effective, exercise intervention programs will be welcome addition to the standard program of care offered to patients with breast cancer receiving chemotherapy.

**Trial registration:**

: National Clinical Trials Number (NCT04867096).

## Background

Breast cancer is the most commonly diagnosed cancer in women, with an incidence of 11.6% worldwide in 2018 [1], although the mortality rate is declining in many developed countries [2]. In breast cancer patients, a common sleep disorder is insomnia [2]. A large, prospective study found that during chemotherapy for breast cancer, 43% of patients met the criteria for insomnia syndrome, and patients with breast cancer had the highest number of overall insomnia complaints [3]. About 40–70% of breast cancer survivors report sleep problems even years after diagnosis, depending on the diagnostic criteria applied [4, 5]. The Diagnostic and Statistical Manual of Mental Disorders, 5th Edition (DSM-5) defines insomnia as a dissatisfaction with sleep quantity or quality, associated with difficulty initiating or maintaining sleep, with the inability to return to sleep, present for at least 3 months, and occurring at least 3 nights per week despite adequate opportunity for sleep [6]. Insomnia can be caused or exacerbated by multiple treatment-related factors, including endocrine therapy and hot flashes, pain and discomfort from local therapy, and fear of recurrence. Insomnia leads to impaired psychological and physical health and may even increase mortality in breast cancer patients [7–9]. Despite its prevalence and impact, insomnia is rarely addressed in the oncology clinic. However, treatment approaches for insomnia are available to clinicians treating patients with breast cancer. There is now a considerable body of evidence supporting the use of psychosocial interventions and behavioral treatments, such as cognitive behavioral therapy for insomnia (CBT-I), yoga, as well as mind-body programs. Indeed, CBT-I is recommended as a first-line treatment for chronic insomnia [10]. Nevertheless, further treatment options for insomnia are necessary, since CBT-I is often unavailable for patients, and may be complex to implement in clinical routine, while poor adherence can decrease its effectiveness [11].

A physical exercise program might be a promising treatment option for preventing cancer-related insomnia, and appears to be safe. Previous studies showed that improved sleep quality positively impacts on quality of life in cancer patients [12] and that the total volume of weekly exercise might influence sleep [13].

Moreover, exercise is recommended during treatment with curative intent. Aerobic and resistance exercise has been shown to reduce fatigue, preserve cardiorespiratory fitness and physical functioning, as well as improve quality of life and depression symptoms [14]. Several trials demonstrated that exercise interventions are feasible in early breast cancer patients and have a low risk of severe adverse events [15, 16].

However, few studies have explored the efficacy of an exercise program for cancer-related insomnia among patients undergoing breast cancer treatments. In this regard, we hypothesize that exercise programs can have a beneficial effect on insomnia for breast cancer patients.

We designed the present randomized FATSOMCAN trial, to examine, in non-metastatic early breast cancer patients with an insomnia diagnosis, the effect on sleep quantity of an individualized, intermittent aerobic exercise training regimen (45 min, 3 times a week), comprising both moderate and high intensity exercise, for a period of 3 months. Secondary objectives are to evaluate the effects of this supervised exercise program on other parameters such as sleep disorders, sleepiness, anxiety/depression, core body temperature and salivary melatonin rhythm. Furthermore, fatigue, pain, inflammatory and cardiorespiratory fitness variables, and level of physical activity (PA) are assessed.

We hypothesize that a supervised exercise program will reduce insomnia and improve the quality and quantity of sleep. Exercise will increase cardio-respiratory fitness, with an improvement in inflammatory variables. We suppose that these modifications will be accompanied by a reduction in sleepiness, anxiety/depression, fatigue and pain. Moreover, we hypothesize that patients who participate in the supervised exercise program will maintain these benefits at the three-month follow-up.

## Methods

The FATSOMCAN study was approved by the Ethics Committee “Comité de Protection des Personnes Ouest III” on 15/09/2020 under the number 2020-A00511-38, and by the National Health Products Safety Agency (N° IDRCB 2020-A00511-38). The study is registered on http://www.clinicaltrials.gov under the identifier NCT04867096. Patient recruitment and data collection started in February 2021. The design of the trial is displayed in Fig. 1.

**Fig. 1 Fig1:**
[figure not shown]
Flowchart for the FATSOMCAN trial

### Recruitment

Six medical oncology centers have been identified in Franche-Comté (France) for the recruitment. Women are recruited and deemed eligible if they meet the following criteria: (1) Aged over 18 and ≤ 65 years; (2) early breast cancer confirmed histologically; (3) undergoing first adjuvant or neoadjuvant sequential chemotherapy with anthracyclines and taxanes; (4) diagnosed as having insomnia; (5) no contraindication to performing physical activity (PA); (6) and either using appropriate contraception or menopaused.

Patients are not eligible in case of: (1) metastases; (2) treatment with melatonin or hypnotics; (3) no diagnosis of insomnia; (4) documented depression; (5) resting oxygen saturation (SaO_2_) ≤ 92%; (6) autoimmune disease (systemic lupus erythematosus, rheumatoid arthritis); (7) symptomatic osteoarthritis, cardiovascular disease (angina or uncontrolled hypertension) or lung disease (chronic obstructive pulmonary disease); (8) malnutrition (body mass index < 18 kg.m^− 2^) or weight loss of > 10% during the previous 3 months; (9) psychiatric or cognitive disorders; (10) pregnant or breastfeeding patients.

Potentially eligible patients are identified during a multidisciplinary tumor board (MTB) composed of oncologists, surgeons and radiotherapists. The choice of the type of surgery, chemotherapy and radiotherapy regimens is left at the discretion of the treating physician.

Potential candidates receive the study information when they come to the hospital for clinical follow-up. If they are interested in participating in the study, a researcher contact them to conduct a phone screen (see below).

Prior to participation, all participants must provide written informed consent.

The participants are instructed to maintain their regular exercise activities, but not to participate in any new exercise program during the study period other than the program proposed in the context of the study.

### Study outcomes

The experimental protocol is described in Fig. 2.

**Fig. 2 Fig2:**
[figure not shown]
Representation of treatment schedule and different times of evaluation and questionnaire completion

At T-1, all potentially eligible patients have a clinical interview according to the DSM-5 to diagnose the presence of insomnia before treatment by chemotherapy. They also complete the study questionnaires [i.e., the Insomnia Severity Index (ISI), the Pittsburgh Sleep Quality Index (PSQI), the Epworth Sleepiness Scale (ESS) and Hospital Anxiety and Depression Scale (HADS)] and a sleep diary for 2 weeks. The interview, questionnaires and sleep diary constitute the baseline values before inclusion. A clinical examination, including medical history, use of analgesics (type, level, dose), lifestyle habits (work, family environment, physical activity, smoking, alcohol), is also carried out.

At T0, one week after completion of the first sequence of the chemotherapy, patients have a clinical interview, complete the questionnaires and sleep diary again. If insomnia is confirmed, patients can then be included.

At T1, at the end of the 3-month exercise intervention (T3) and at 6 months (T6) of the follow up period, objective sleep parameters, salivary melatonin and core body temperature rhythm are evaluated. At T1 and T3, fatigue, pain, inflammatory variables and cardiorespiratory fitness are assessed. At T3, DMS-5 interview, questionnaires and sleep diary are completed again. From T1 to T6, the level of PA is followed (Fig. 2).

### Randomization

At T1, patients are randomly assigned (in a 1:1 ratio) to one of the two groups, namely either to receive standard oncological care alone (Control Group: CG) or standard care plus an exercise program (Training Group: TG), which starts at the halfway point through the chemotherapy protocol. During the follow-up period (T3-T6), both groups follow standard oncological care without supervised PA. Furthermore, the level of PA, without guidelines, is assessed by a connected watch.

### Primary endpoint

The primary endpoint is a reduction in insomnia assessed by an increase in total sleep time (TST).

### Secondary endpoints

Secondary endpoints are a decrease of insomnia severity, an improvement in sleep quality, a decrease in sleepiness, anxiety/depression, pain, fatigue, inflammatory variables, and an enhancement of cardiorespiratory fitness.

#### Sleep architecture and composition

Sleep architecture and composition are assessed by an ambulatory polysomnography, which represents the gold standard to objectively measure TST, sleep patterns and diagnose sleep disorders (e.g., obstructive sleep apnea, periodic limb movements). Patients undergo one night of home-based polysomnography (PSG) (Morpheus, Micromed, Italy). Sleep is assessed with standard PSG techniques using the 10–20 system [17]. The following variables are continuously measured and recorded throughout the night: Fz, Cz, F4-M1, C4-M1, O2-M1, F3-M2, C3-M2 and O1-M2, left and right electrooculogram, chin electromyogram, left and right anterior tibialis electromyogram and electrocardiogram.

Hypopnea, obstructive and central apnea are assessed thanks to respiratory efforts with thoracic, abdominal inductance plethysmography (SleepSense, S.L.P. Inc., Elgin IL 60,124 USA) and with airflow, which is measured by a nasal pressure cannula (ThermoCan, SleepSense, S.L.P Inc., Elgin, IL, USA). Snoring is scored by filtration of the nasal pressure signal. Peripheral oxygen saturation (SpO_2_) and heart rate (HR) are recorded by pulse oximetry (Nonin medical, Inc. Plymouth, MN, USA). A sensor is placed on the chest and enables detection of the body position during recording.

Patients are instructed to maintain their habitual sleep patterns and asked to record the time of lights-out and the time immediately upon waking the next morning. PSG data are recorded directly to a data acquisition, storage, and analysis system (SleepRT™ software Suite Version 4.04.02 Buil5185; OSG, Belgium). The electroencephalogram (EEG) recordings are visually scored in 30-second periods, to obtain the overnight pattern of sleep stages, and respiratory events in 3-min periods for airflow by an experienced board-certified sleep physician using the American Academy of Sleep Medicine’s standard rules.

The following sleep parameters are recorded: bedtime (h:min), wake-up time (h:min), time in bed (TIB, h), total sleep time (TST, h), sleep efficiency (SE, %), sleep onset latency (SOL, min, time from lights out to sleep onset, defined as the 1st epoch of any sleep stage (min), wake after sleep onset (WASO, min, number of minutes scored as wake-up time during sleep period, min), number of awakenings (nb), awake time (%), total time in stage 1 sleep (TTN1, min), percentage of stage 1 sleep in TST (N1, %), total time in stage 2 sleep (TTN2, min), percentage of stage 2 sleep in TST (N2, %), total time in stage 3 sleep (TTN3, min), percentage of stage 3 sleep in TST (N3, %), total time in rapid-eye movement sleep (TTREM, min) and percentage of REM sleep stage in TST (REM, %).

#### Objective sleep parameters

Patients wear an actimeter on their non-dominant wrist (ActiGraph® GT3X-BT, Pensacola, FL, USA) from bedtime until waking up, for seven consecutive nights. A sleep diary is used, as a complement to actigraphy, to determine when patients are awake and when they are lying down attempting to sleep. The sleep diary collects habits and sleep hygiene over an extended period of two weeks. Patients indicate bedtime, wake-up time, awakenings, periods of sleep and sleepiness, and consumption of drugs. In addition, the subjective quality of sleep and awakening are indicated.

Data from actigraphy are downloaded and analyzed on ActiLife software (ActiGraph®, Pensacola, FL, USA). All records are scored as asleep unless the sleep diary indicates that the patient is lying in bed attempting to sleep. Data are downloaded and analyzed using the Cole-Kripke algorithm on ActiLife software in 60 s epochs. Once the bedtime and wake-up time are defined, automatic Cole-Kripke algorithm analyses are run to extract the following sleep parameters: bedtime (h:min), wake-up time (h:min), SOL (the first minute that the algorithm scores “asleep”), TIB, TST, WASO, awakenings (the number of different awakening episodes as scored by the algorithm), average awakening (the average length, in minutes, of all awakening episodes), total counts (the total actigraphy counts summed together for the entire sleep period), sleep efficiency (SE, number of sleep minutes divided by the total number of minutes the subject is in bed x 100: TST/TIB x 100).

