## Statistical analyses

### Sample size

To detect a difference of TST of 10% compared to baseline value (considering a TST of 420 min), between the two groups, at T3, a Z-test with a type I error of 5% and a statistical power of 80% will be used. A total of 57 patients including 29 in CG and 28 in TG are required.

Two interim analyses for the efficacy and futility using the Lan-Demets method (O’Brien Fleming boundaries) to estimate the alpha spending function will be performed at 33% and 66% of the information fraction (after enrolment of 19 and 38 evaluable patients). With 10% of non-evaluable patients, 64 patients should be randomized. The primary objective will be done in modified intention-to-treat (miTT): all randomized and evaluable patients for the TST at T0 and T3.

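### The actigraphy scoring sentence is inverted and contradicts its own section; followed literally, it would count recorded night-time minutes not spent trying to sleep as sleep

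*Protocol article*

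**What the plan says.** All of the scoring text is in the protocol article, Methods, under Objective sleep parameters.

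- **Wear.** The actimeter is worn "from bedtime until waking up, for seven consecutive nights".
- **Diary.** A sleep diary complements it, "to determine when patients are awake and when they are lying down attempting to sleep". The listed entries are bedtime, wake-up time, awakenings, periods of sleep and sleepiness, drug consumption, and subjective quality of sleep and awakening.
- **Default rule.** "All records are scored as asleep unless the sleep diary indicates that the patient is lying in bed attempting to sleep".
- **Algorithm.** Data are then analysed with Cole-Kripke in 60-second epochs: "Once the bedtime and wake-up time are defined, automatic Cole-Kripke algorithm analyses are run to extract the following sleep parameters". The parameters include sleep onset latency, TST, wake after sleep onset (WASO) and awakenings.
- **Sleep efficiency (SE).** It is the "number of sleep minutes divided by the total number of minutes the subject is in bed x 100: TST/TIB x 100".

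Two other places matter. The Primary endpoint section defines success as an increase in TST and names no instrument. The section on sleep architecture describes one night of home polysomnography, "which represents the gold standard to objectively measure TST".

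**The concern.** A default rule decides what happens to every recorded minute that the diary does not place in bed and trying to sleep. The natural default for such minutes is awake; the article says asleep. A scorer who followed it would credit sleep to a patient who was up during the night.

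Actigraphic TST, SE and WASO would all be affected. All enrolled patients have insomnia, and the article's own description of insomnia includes nocturnal awakening, so time out of bed at night is plausible in this population. The rule is explicit in the Methods, so this is not detail that a condensed article has left to a fuller document.

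**Working it through.** The document gives no figure that depends on this rule, so there is none to reproduce. The check sets the statements of the section side by side and then follows the literal rule through to the outcomes.

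**1. Default rule against the diary's purpose.** The diary separates two states: awake, and lying down trying to sleep. Time outside the second state is therefore awake. The default rule assigns that same time to sleep. Both statements cannot hold.

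**2. Default rule against the algorithm step.** Cole-Kripke runs after bedtime and wake-up time are fixed, and its output is the source of latency, TST, WASO and awakenings. So the window of attempted sleep is where sleep may be found. The default rule makes that window the exception to being asleep. It also does not say how the excepted minutes are scored; the only workable reading is that the algorithm scores them. The text does not say which statement prevails if the two disagree.

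**3. What the literal rule can reach.** The device is worn only from bedtime to waking, so daytime is not at issue. What remains is recorded night-time when the patient is not in bed attempting to sleep. Call this *m* minutes per night.

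**4. Effect within one patient.**

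- TST (literal) = TST (awake by default) + *m*
- SE (literal) = (TST + *m*) / TIB × 100, where TIB is time in bed
- WASO falls by those of the *m* minutes that come after sleep onset

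The document gives no value for *m*. Assumed for illustration: TIB 480 min and 400 min of true sleep in bed, so SE = 400/480 = 83.3% with awake as default. The last column sets *m* against the difference in the Sample size section, 10% of 420 min = 42 min, for scale only.

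| *m* (assumed, min) | TST, literal rule (min) | SE, literal rule | *m*/42 |
|---|---|---|---|
| 10 | 410 | 85.4% | 0.24 |
| 20 | 420 | 87.5% | 0.48 |
| 30 | 430 | 89.6% | 0.71 |
| 45 | 445 | 92.7% | 1.07 |
| 60 | 460 | 95.8% | 1.43 |

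If out-of-bed minutes are left out of TIB but counted as sleep, SE would exceed 100% once *m* passes 480 − 400 = 80 min. With awake as the default, the error from this source is 0.

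**5. Effect on the comparison between arms.** Observed difference (training minus control) = true difference + (mean *m* in training − mean *m* in control). With assumed values and a true difference of 42 min:

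- equal *m* in both arms: 42 + 0 = 42 min, no bias
- training 10, control 30: 42 − 20 = 22 min
- training 30, control 10: 42 + 20 = 62 min

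The document gives no basis for choosing among these.

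**The case against.** The strongest reply is that the sentence is a one-word slip for awake and has no effect in practice. The sentences after it describe automatic scoring in software. Latency is defined by the first minute the algorithm scores as sleep, and awakenings are those the algorithm scores. Minutes before bedtime or after wake-up have no described route into TST. Leaving the bed is not among the listed diary entries, and no manual override of the algorithm is described. Nothing shows that any file was scored in the inverted way.

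Most of this stands. It limits the consequence and makes a drafting slip likely. It does not remove the contradiction: the article states two incompatible rules and does not rank them, so actigraphic TST cannot be reproduced from the text.

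A reader might go further and infer that the rule hides a treatment effect, for example by removing 20 of 42 min (20/42 = 48%) if controls were out of bed for 30 min and trained patients for 10. The documents do not support that. Both times are assumed, and the loss comes entirely from the assumed gap between arms.

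A reader might also infer that the primary endpoint is compromised. That is not shown either. The 42 min belongs to the primary endpoint, whose TST may come from polysomnography, and this rule does not touch polysomnography.

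**Conclusion.** The actigraphy default rule is wrong as written. It reverses the diary's stated purpose and conflicts with the Cole-Kripke step in the same section, and no other part of the article corrects it.

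The consequence is conditional. If the rule was applied literally, actigraphic TST rises minute for minute with recorded night-time not spent in bed attempting sleep, SE rises with it, and WASO falls. If the algorithm alone scored each epoch between bedtime and wake-up, only the wording is at fault. Neither the size nor the direction of a between-arm bias can be derived, because no times out of bed are given. The primary endpoint is affected only if its TST is taken from actigraphy, on which the Primary endpoint section is silent.

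**What to change.** In the default-rule sentence, replace asleep with awake, and add that within the diary-defined window of attempted sleep the Cole-Kripke algorithm scores each epoch. This makes the sentence agree with the rest of the section.

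Data collection began in February 2021, so some files may already be scored. Confirm that they followed the corrected rule, and rescore only those that did not.

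The cost is one sentence and a check of stored actigraphy files. Rescoring arises only if the check finds files processed under the literal rule, and it needs no new data from patients.

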#### Insomnia evaluation

Insomnia is diagnosed per patient-reported symptoms in accordance with criteria from the DSM-5 [6]. DSM-5 classifies insomnia as a subjective complaint with difficulty falling asleep and/or nocturnal awakening and/or early waking despite adequate opportunity for sleep. This condition causes distress and impairment in daytime functioning such as fatigue/low energy, daytime sleepiness, impaired attention/concentration, mood disturbances, amongst other impairments. These disturbances with sleep are not related to any other medical disorder, substance use, or prescription use, and the symptoms must be present at least three nights per week for at least three months.

Insomnia is also assessed using the Insomnia Severity Index (ISI). The ISI is a valid diagnostic screening tool for detecting insomnia and correctly identifies people with DSM-5 defined insomnia disorder [18]. It has also been validated in cancer populations [19]. The ISI comprises seven items that assess the severity of sleep-onset and sleep-maintenance difficulties (both nocturnal and early morning awakening), satisfaction with current sleep pattern, interference with daily functioning, noticeability of impairment attributed to the sleep problem and degree of distress or concern caused by the sleep problem [20, 21]. Each item is rated on a five-point Likert scale (0 = not at all; 4 = extremely) and the usual recall of the “last month”. Total scores range from 0 to 28 with high scores indicating the greatest insomnia severity. The total score is interpreted as follows: absence of insomnia (from 0 to 7); sub-threshold insomnia (from 8 to14); moderate insomnia (from 15 to 21) and severe insomnia (from 22 to 28).

